## Discussion

5

This study provides the opportunity to utilize a quasi-experimental framework to begin to understand how sex-specific vulnerabilities may be associated with educational opportunities in adolescence that will impact physical health risks and cognition in early adulthood, ultimately setting the stage for AD risk later in life. We expect that sex-specific vulnerabilities related to mobility opportunity in adolescence will increase physical health risks in early adulthood: increased inflammation and altered microbiome, specifically in females. We hypothesize that, in turn, a female's physical health risks will be related to their cognitive performance in young adulthood and to the neural underpinnings of those cognitive skills, revealing early indicators of AD risk after education opportunities. In other words, we suggest that the differential impact of high-performance schooling on physical health in females and males may undo the cognitive resilience generated through better education in females. Additionally, we will explore how education opportunities in adolescence interact with genetic vulnerabilities for AD - *ApoE-ε4* – for example, it is possible that striving-related stress may undo some of the cognitive benefits of educational opportunity via health pathways in females, which may in turn relate to their cognitive outcomes and neural correlates therein. By investigating the impact of schooling on inflammation and microbiome profiles in young adulthood, this study will reveal potential developmental mechanistic pathways that might be linked and contribute to AD outcomes much later in life.

Striving for better educational attainment during adolescence can be stressful for youth, seemingly more so for females, and this striving-related stress may induce consequential health problems, such as increased systemic inflammation, altered brain-gut axis signaling and other neurotoxic effects, including neuroinflammation, impacting later cognitive outcomes and AD risk. An overarching goal of this study is to critically consider and examine the potential health costs from psychosocial factors—such as stress and educational attainment—in diverse youth early in life. By pursuing this research, we may be able to assess in the future whether intervening and improving factors earlier in development, such as education and educational settings by improving and increasing support and resources while youth are striving, can ultimately impact and set the stage for health outcomes across the lifespan and later illness risk. It is critically important to note that our findings would reveal what kinds of support are needed, particularly for females early in life, to ensure such pursuits for improved future socioeconomic attainment do not evoke unintended and deleterious health consequences. In addition to increasing and maintaining cognitive reserves by improving education attainment as an important and feasible early prevention strategy for AD, prior work has also identified that reducing risk for neuropathological damage is important for slowing progression and prevention (Zhang et al., 2021). Therefore identifying early indicators and biological mechanisms of AD and related dementias is important for modulating disease development and outcomes. The presence of A β plaques and neurofibrillary tangles are both core features of the brain pathology that characterizes AD. Understanding the biological mediators, such as peripheral and central inflammation and altered gut-brain-axis signaling, that impact onset, generation and progression of these pathologies in AD is important to improve health outcomes and reduce risk.

A strength of the RISE-Up study is its quasi-experimental design through random admissions lottery to several charter schools allowing us to sample comparable cohorts of adolescents exposed to different school environments and thus, more rigorously test the causal effect of exposure to high-performing schools on health and cognition. This design avoids the limitations of observational studies assessing health and education and allows for more control over confounding variables, such poverty, neighborhood, and family factors (Cutler and Lleras-Muney, 2006, 2010; Galama et al., 2017). One limitation of the data collected thus far in the RISE-Up cohort is its reliance on self-reported health data. The addition of objective markers of health (e.g., microbiome and inflammation) in the follow up timepoints will greatly add to the rigor of this study and expand the research scope. Furthermore, little is known about risk factors for AD that may be unfolding during young adulthood despite the knowledge that this is a pivotal period for physical and mental health. In general, more research is also needed to determine more consistent evidence for sex and gender differences in risk pathways for AD. However, the research conducted thus far highlights the urgent need to understand how and why potential modifiable risk factors modulate the risk and progression of AD, and how they can be leveraged to reduce AD risk for all. Therefore, it is critically important to assess how sex interacts with potential mechanisms that contribute to increased health risks, especially earlier in life, that may inform vulnerabilities for AD. Therefore, this study has unprecedented opportunity to identify mechanisms and explicitly assess sex-specific vulnerabilities that may in turn be used to identify optimal windows for prevention or invention efforts that optimize cognitive and physical health outcomes in youth striving for upward mobility from low socioeconomic status backgrounds.

The RISE-Up EA + study adds an additional timepoint of data collection to the longitudinal RISE-Up Study in early adulthood with neurobiological data targeting the brain-gut axis, to allow us to rigorously test causal effects of exposure to high-performing schools on health, brain-gut signaling, and cognition outcomes in early adulthood, which may set the stage for later AD risk. The overall goals of this project are to elucidate how adolescent mobility opportunities will be tied to later cognitive and brain health outcomes in young adulthood via sex-specific changes to potential biological mediators—inflammation and gut-brain-axis—to inform vulnerabilities for developing AD later in life. This study seeks to discern causal links between education and health by taking an innovative approach by assessing early developmental pathways that may set the stage and be linked to AD risk later in life. By identifying early markers before AD manifests, we can work to improve resilience pathways and decrease risk pathways to improve health outcomes and functioning in later adulthood. Supporting youth socioeconomic development and socioeducational success is extremely important. This research aims to find modifiable factors to improve health outcomes and support youth early in life so that everyone can reap the benefits that high quality education has to offer while reducing potential negative health consequences that may accompany sex-specific development.

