The RISE-Up EA+ study leverages a natural quasi-experimental cohort that began in 2013 (RISE-Up) to understand the impact of educational experience on youth health outcomes and substance use (R01DA033362). The random admissions lottery of five high-performing charter schools in Los Angeles was initially used to find two comparable groups of adolescents that were exposed to high-and lower-performing public high schools. These groups had similar baseline demographics, prior academic performance, family characteristics, and neighborhood exposures, and have been followed longitudinally during adolescence from ages 13 through 18 (phase 1: RISE-Up-HS; R01DA033362), during their transition to emerging adulthood from ages 18 through 24 (phase 2: RISE-Up-T2A; R01DA033362), and into early adulthood from ages 24 through 28 (RISE-Up EA; R01A082868) while collecting various self-reported health metrics to understand the impact of education on health outcomes (see Fig. 1 for a timeline of study phases). (Wong et al., 2014, 2022) To assess cognitive ability and brain health, as well as associated inflammatory and microbiome-related biology, we will conduct an add on to the RISE-Up EA study (called RISE-Up EA+) to collect additional cognitive and neurobiological measures after participants began enrollment in RISE-Up EA when the cohort is aged between 24 and 26 years. Findings from earlier timepoints in the RISE-Up study position it to address the unique question of how sex-related AD risk may manifest across the lifespan. Specifically, earlier waves from grade 9 through grade 11 (RISE-Up-HS) identified that adolescents attending high-performing schools were less likely than those in lower-performing schools to engage in risky substance use and have substance using peers in their social network (Dudovitz et al., 2018). Recent results also show that young adults aged 20 and 21 (RISE-Up-T2A) that attended high-performing schools had lower rates of hazardous or dependent alcohol use, had lower cannabis misuse scores, less delinquent behaviors, and higher rates of fair/poor mental health scores (Wong et al., 2022). Differences in physical health outcomes were found between males and females, where rates of fair/poor physical health and overweight/obesity were lower for young adult males that attended high-performing schools but higher rates were found for young adult females (Wong et al., 2022). Controlling for academic outcomes (e.g., high school graduation and grade point average, standardized test scores and college matriculation) had no impact. This may indicate that the developmental pathways for later AD risk may already be in motion for females with greater mobility opportunity in the RISE-Up study (Wong et al., 2022). However, the precise biological mechanisms informing this risk are still unclear. In this paper, we will summarize the study aims, hypotheses, and protocol for the RISE-Up EA+ Study that aims to understand how factors contributing to health after mobility opportunity impact sex-related risk for developing AD later in life.

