### Recruitment & eligibility

3.1

The demographics of the original RISE-Up Study have been described extensively elsewhere (Wong et al., 2022; Dudovitz et al., 2018), but broadly consisted of 1270 participants (52.6% female, 47.4% male, median age 14.2) who were entering 9th grade in Fall 2013 or Fall 2014. Participants for the original study were largely recruited from and are representative of low-income neighborhoods in Los Angeles, with 1137 (89.5%) identifying as Latino (Dudovitz et al., 2018), and all applied for high-achieving charter high school admission lottery, with 694 students (54.6%) being admitted on the basis of random lottery (intervention/mobile group) and 576 students (45.4%) on the waiting list (control/static group). Recruitment for the RISE-Up-EA+ extension study is dependent upon previous participation in the RISE-Up-EA follow up study, which is ongoing (see Fig. 1 for a timeline of study phases). A subsample of 300 participants aged 24-26 years old who previously consented to follow-up contact will be included in the extension study. Detailed contact information has been maintained for prior participants, enabling digital communication via text message and email. Interested respondents will schedule a phone screening, during which a study coordinator will administer a brief screening interview and obtain informed consent. During this phone screen, the research staff will also explain procedures for the extension study. Participants who meet eligibility criteria for the study (including MRI safety screening) and agree to participate will be scheduled for a three and a half hour on-site in-person session at the University of California, Los Angeles (UCLA) where they will complete a magnetic resonance imaging (MRI) scan, behavioral tasks, cognitive assessments, and will be administered biospecimen samples (see Fig. 3 for session flow). Prior to their in-person session, participants will be consented and will be administered questionnaires to complete remotely or they will have the opportunity to complete questionnaires at the in-person session. The protocol for this study has been approved by the Medical Institutional Review Board of the University of California, Los Angeles (IRB#24-000281).

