**Fig. 3 fig3:**
[figure not shown]
*The RISE-Up EA+ In-Person Session Flow.* Eligible participants will be scheduled for in-person sessions at UCLA. During the pre-scan section of the session, participants will review consent forms, complete updated MRI safety screening forms, and will be trained on fMRI tasks that they will complete inside the scanner. During the MRI scan, we will collect multimodal imaging data including structural, functional, and neurometabolic data. After the scan, participants will contribute biological samples, complete the NIH-Toolbox, and provide self-report questionnaires if these were not completed prior to the in-person session. Created in https://BioRender.com.

*Exclusion Criteria:* Exclusionary criteria include typical MRI contraindications (e.g., the presence of braces or metal implants). Due to the requirements of an in-person study visit, previously-enrolled participants who have relocated out of state will be excluded. Since the original RISE-Up study's inception, only 30 participants (2.4%) have moved entirely out of California.

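### The lottery makes 1,270 pupils comparable, but the 300 analysed are selected after it, and the causal claim carries no caveat for that selection

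*Protocol article*

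**What the plan says.** Section 1.7 rests the design on the lottery: "The random admissions lottery of five high-performing charter schools in Los Angeles was initially used to find two comparable groups of adolescents". It then describes how alike the groups were: "These groups had similar baseline demographics, prior academic performance, family characteristics, and neighborhood exposures". Section 3.1 gives their size: "1270 participants (52.6% female, 47.4% male, median age 14.2) who were entering 9th grade in Fall 2013 or Fall 2014", "with 694 students (54.6%) being admitted on the basis of random lottery (intervention/mobile group) and 576 students (45.4%) on the waiting list".

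The extension is much smaller: "A subsample of 300 participants aged 24-26 years old who previously consented to follow-up contact will be included in the extension study". Section 3.1 also requires earlier participation in the early-adulthood phase (target 750 in the Fig. 1 legend), a response from those interested, and MRI safety screening. The exclusion criteria add that "previously-enrolled participants who have relocated out of state will be excluded", and note that only 30 people (2.4%) have left California.

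The Discussion then makes two claims. On the RISE-Up design: "This design avoids the limitations of observational studies assessing health and education". On the extension: "to allow us to rigorously test causal effects of exposure to high-performing schools on health, brain-gut signaling, and cognition outcomes in early adulthood". The limitation it names for the cohort's data so far is reliance on self-reported health. It does not mention selection into the 300.

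**The concern.** A lottery balances known and unknown factors in the people who entered it. It does not do so for a subset formed years later by steps that may depend on the lottery result. If those steps favour different kinds of people in the two groups, winners and waitlisted participants in the 300 can differ before any school effect is considered.

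The article itself gives reasons to expect such dependence. Sections 1.4 and 1.7 report group differences in substance use, delinquency and mental health. They also report differences in overweight/obesity and physical health that run in opposite directions for females and males. Such traits could plausibly affect who stays in contact, volunteers and can be scanned.

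The sex pattern matters most. Aim 1 asks whether the effect of mobility opportunity differs by sex. The bias in that contrast is the bias among females minus the bias among males, so selection running in opposite directions by sex would add up and not cancel. A finding of this kind would be reported as causal.

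**Working it through.** **Inputs from the article.** Cohort 1,270 = 694 + 576 (Section 3.1). Early-adulthood target 750 (Fig. 1 legend). Extension 300 (Section 3.1). 150 per group, two-sided alpha .025, 80% power, d = 0.36 (Section 4).

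**1. The plan's own figure.** Two independent groups of 150 at two-sided alpha .025 have critical t = 2.253. Solving the noncentral t for 80% power gives d = 0.3575 with noncentrality 3.096. This reproduces the stated d = 0.36, 2.25 and 3.10, so d = 0.36 is a sound yardstick for a two-group difference.

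**2. How selected the sample is.**
- 300/1270 = 23.6%; 300/750 = 40.0%.
- Winners: 150/694 = 21.6%. Waitlisted: 150/576 = 26.0%.
- Left the state: 30/1270 = 2.4%, so relocation is a minor step.

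**3. What selection could do (assumed values).** The article gives no participation by group, so this shows a range and estimates nothing. Let X be a baseline trait with mean 0 and SD 1, and let participation follow logit P = a + b·X, with b = ln(OR) and a set to give the stated participation fraction. The mean of X among participants is E[X·P(X)] / E[P(X)].

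| Scenario | OR per SD | Group difference in X |
|---|---|---|
| One group only, 23.6% take part | 1.25 | 0.17 SD |
| One group only, 23.6% | 1.5 | 0.30 SD |
| One group only, 23.6% | 2.0 | 0.49 SD |
| One group only, 59.1% (750/1270) | 1.5 | 0.16 SD |
| Both groups, 21.6% and 26.0% | 1.5 | 0.309 − 0.291 = 0.02 SD |
| Participation unrelated to X | 1.0 | 0 |

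The 59.1% row covers the case in which the trait drives only entry to the 750 and the cut to 300 is just the planned sample size.

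**4. On the outcome scale.** With an assumed correlation of 0.5 between X and the outcome, and no adjustment, bias = 0.5 × difference:
- One group only at 23.6%: 0.08, 0.15 and 0.24 SD. The middle value is 0.15/0.36 = 42% of the detectable effect.
- One group only at 59.1%, OR 1.5: 0.08 SD.
- Both groups, OR 1.5: 0.01 SD.

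With 150 per group, a spurious shift of 0.15 SD raises the false-positive rate from 2.5% to about 17%.

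**The case against.** The strongest reply is that this is a condensed article. Balance tables, weights and model terms commonly sit in the full protocol or analysis plan, and their absence is no fault. That stands. The point therefore rests on what the Discussion asserts, not on what the article leaves out.

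The second reply is that the wording is softer elsewhere. The article calls the design quasi-experimental, speaks of more control over confounding, and frames H1 and H1.2 as associations. This is fair, but the two Discussion statements are unqualified, and the second is about the extension itself.

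The third reply is that the larger figures assume selection in one group only with no adjustment. That also stands: the range starts at zero.

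A reader might infer more than the documents support:
- *That the analysis is a plain pooled comparison of 150 with 150.* Section 4 uses the t-test only to approximate power. It names random effects general linear models, whose random terms are not specified and could carry school or entry year.
- *That there were five separate lotteries with unequal odds.* Section 1.7 speaks of the admissions lottery of five schools and gives no odds by school or year. Pooling causes no bias if win rates are equal.
- *That participants had to stay through the transition phase (977).* The Fig. 1 legend says the early-adulthood phase recruits from baseline participants.
- *That school attendance replaces the lottery result as the exposure.* Section 3.1 defines the groups by lottery admission and waiting list.
- *That the estimates are biased.* No participation or balance data by group are given for the 300.

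**Conclusion.** The concern holds as an overclaim. The article asserts for the 300 a protection that the lottery gives only to the 1,270. With 23.6% entering through post-lottery steps, comparability in the extension depends on an assumption about participation that the Discussion does not state.

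The size of any bias is unknown. On the assumptions above, the groups could differ by anything from zero to about 0.49 SD on a single trait. Bias is material only if participation depends on outcome-related traits differently in the two groups, or differently by group and sex for the moderation question. It is worth correcting because sex moderation is the main question and the remedy needs no new data collection.

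**What to change.** Using the baseline data held on the original cohort:

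1. Show baseline balance by lottery group and sex for the 300, beside the same table for the 1,270.
2. Adjust the main models for prognostic baseline variables such as prior achievement, family and neighbourhood measures.
3. Add an analysis with stabilised inverse-probability-of-participation weights. Model participation on group, sex, their interaction and baseline variables.
4. Include lottery school and entry year (2013 or 2014) in the model, if the random effects do not already carry them.
5. Reword the two Discussion statements so that the causal claim for the 300 is conditional on no unmeasured selection into the extension.

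This is analysis and wording work on existing data. The price is some loss of precision from weighting and a softer causal claim. Weighting corrects only for selection on measured variables, which is why the rewording is needed as well.

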## Data Availability

No data was used for the research described in the article.
